## Abstract

**Background:**

Although internet-based stress management programs are proven effective in improving mental health among workers, micro- and small-sized enterprises (MSEs), lacking in occupational healthcare services, face challenges implementing them. To address this gap, this study will develop the program with stakeholders at MSEs to aim for real-world implementation.

**Objectives:**

This paper describes a study protocol for a pre-post feasibility study of an effectiveness-implementation hybrid type 2 trial of text-based internet-based programs (“WellBe-LINE”) in MSEs with less than 50 employees. This feasibility study primarily aims to evaluate trial methods for future effectiveness-implementation hybrid type 2 trials.

**Methods:**

For this study protocol, an internet- and text-based self-care intervention program using the LINE app (a popular message tool in Japan) will be prepared according to evidence-based psychoeducational topics. Based on our online survey findings, personalized algorithms will be implemented according to employees’ gender, age, and psychological distress levels. A personalized program using a popular pre-existing text app is expected to reduce employees’ burdens and be attractive to them, resulting in successful implementation outcomes and mental health benefits. A pre-post design feasibility study will be conducted on ten companies to evaluate trial methods (e.g., recruitment and procedures). The primary outcome will involve individual-level penetration, defined as the proportion of the number of employees who register for the program divided by the total number of invited employees at the company. The progression criterion to go next trial specifies that more than 50% of the recruited companies obtain 60% individual penetration, which is set based on the findings of the prior survey of employees at MSEs and of interviews of stakeholders involved in this study, and will be measured by LINE system. Finally, acceptability, appropriateness, and feasibility will be measured using internet-based questionnaires and interviews.

**Discussion:**

This pre-post feasibility study for future effectiveness-implementation hybrid type 2 trials will provide in-depth knowledge about the successful implementation of text-based, semi-personalized, self-care mental health interventions in real-world settings using both quantitative and qualitative data.

**Conclusions:**

This feasibility study will help validate the effectiveness of text-based interventions using a widely used social networking service (SNS) tool for employees in MSEs.

**Trial registration:**

UMIN clinical trial registration, UMIN000046960. Registered on February 21, 2022.

https://center6.umin.ac.jp/cgi-open-bin/ctr/ctr_view.cgi?recptno=R000053570

**Supplementary Information:**

The online version contains supplementary material available at 10.1186/s40814-024-01481-9.

## Contributions to the literature

Internet-based mental health interventions in micro- and small-sized enterprises have not been implemented yet.This feasibility study plans to test the implementation strategies to achieve high penetration in employees.This study can provide insights into occupational health implementation in a disadvantaged context.

## Background

Worldwide, mental health problems in the workplace impact individual health-related disability and productivity loss [1, 2]. Micro-, small-, or medium-sized enterprises (MSMEs) are important targets for mental health interventions [3] as they represent about 90% of businesses and more than 50% of employment worldwide [4]. However, MSMEs, especially micro- and small-sized enterprises (MSEs) with fewer than 50 employees, are less likely to implement health promotion programs because of limited resources, such as cost, access, and time [5]. Thus, offering evidence-based programs alone may not be valuable for employees. While implementing the primary prevention of mental health in MSMEs is challenging [3], preventive interventions for mental health is generally more effective when used by a large population [6]. Therefore, increasing the adoption and penetration (reach) of health promotion program is  the key objective. To achieve high penetration, interventions and strategies specific for MSEs must consider implementation barriers.

Previous studies have identified barriers to the implementation of mental and health interventions in small companies [7–12]: low leadership engagement of employers [7], lack of knowledge about the impact on business [8], limited resources [9, 12], limited time and money [11], regulations (no legal requirement) [12], lack of understanding on the necessity of the interventions, and suboptimal approach [10]. Additionally, job-related stressors between small and large companies varied [13]. In small companies, poor psychosocial factors at work and poor communication are strongly associated with job stress [13]. Therefore, personalized intervention content and specific delivery strategies to overcome organizational barriers in MSEs are needed.

Internet-based interventions are potential options to solve problems of implementing mental health interventions in MSEs, considering high ownership rate of smartphone in Japan. Internet-based intervention is feasible, cost-effective, and accessible [14–16], meeting the needs and addressing the low resource (i.e., limited time and money, lack of human resource and occupational health services) at MSEs. A comparison of face-to-face and internet-based interventions revealed no differences in their effectiveness in treating common mental disorders [17, 18]. Even text message-delivered interventions have been proven to be effective for stress management [19]. Including the occupational health settings, the effectiveness of the internet-based interventions without a face-to-face component has been shown in meta-analysis [15, 16].

Moreover, tailoring (or personalizing) messages in internet-based interventions proves even more effective in stimulating changes in health behavior [20]. Internet-based and personalized text message interventions may thus be suitable for improving the acceptance of employees, leading to successful implementation in MSEs. Low-intensity programs can alleviate the burden on workers, and personalized online programs with ease can effectively address stigma at MSEs. Additionally, programs presented in easily understandable language address a wide variety of employees’ knowledge about mental health, resulting in acceptability. Acceptability, appropriateness, and feasibility have been suggested as important implementation aspects of mental health interventions [21–24]. However, few studies have not been conducted yet examined the effectiveness and implementation outcomes of internet-based interventions for MSEs without some recent protocols [25, 26]. Therefore, methods to improve implementation outcomes (i.e., implementation strategy) should be developed and examined.

As MSME managers have little motivation to implement the program [5, 7], a specific implementation strategy personalized to the context should be adopted. According to the Expert Recommendations for Implementing Change (ERIC), educating stakeholders (employees, employers/managers, and recruiters) is a possible strategy if leadership engagement can be a barrier in the context [27, 28].

Informing employers about the importance of preventive measures in mental health and effective procedures for introducing the program to employees may increase their adoption. However, no study has investigated the effect of internet-based interventions on MSEs with such implementation strategies (i.e., educating employers). Previous implementation research for mental health interventions using the internet or technologies suggested the negative attitude of stakeholders (and, particularly, the users) for internet-based interventions (more preference for face-to-face) [29, 30] and require education for providers [31]

Hybrid-type designed studies can be conducted between effectiveness studies and implementation research [32]. The hybrid type 2 design can be used to test the effectiveness in general practice settings without controlling/ensuring delivery of the intervention and implementation process [32]. Moreover, feasibility and pilot studies [33] can help build and test effective implementation strategies by addressing uncertainties around design and methods and identifying potential causal mechanisms [34]. According to the CONSORT 2010 statement: extension to randomized pilot and feasibility trials, pilot or feasibility studies should have clear criteria for deciding whether to progress to the next full trial [35, 36]. Because there are still many uncertainties in MSEs settings and less evidence is available in implementation research, a pilot feasibility study is important to obtain insights about how we should act in the next stage.

### Aims and objectives

This pre-post feasibility study on a future effectiveness-implementation hybrid type 2 trial aims to evaluate the implementation trial procedures of text-based online programs in micro- and small-sized enterprises with less than 50 employees.

The objectives of this feasibility study, in preparation for a future trial, are as follows:To evaluate the feasibility of trial methods (e.g., recruitment, and procedures) and strategies by setting individual-level penetration as an indicator of successful implementation (primary outcome).To evaluate the barriers and facilitators at MSEs to increase individual-level penetration for revising the strategies.To evaluate the acceptability, appropriateness, and feasibility of the program among recruiters, employers/managers, and users.To evaluate the fidelity and cost of delivering the program to employees among recruiters and employers/managers.To ensure no harm on psychological distress of the users.

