#### Process outcome

Block rate

LINE accounts can reject or “block” contact from other accounts. We will assess this rate of blocking by system detection.Uncomfortable experience/harms

Uncomfortable experience/harm will be assessed using five items from the iOSDMH [24]. Time consumption, mental symptoms, induced dangerous experiences regarding safety, physical symptoms, and excessive pressure on regular learning will be measured for employees (users) in the questionnaire. Employers/managers and recruiters will be asked to rate the following item: “This program does not result in negative side effects (e.g., physical or psychological symptoms).” The response options are 4-point rating scales for users and 5-point rating scales for providers (managers or policy makers), with the added option of “Don’t know.”Adherence (completion rate)

Whether employees read or engaged with messages could not be accurately detected in LINE owing to technical limitations. Instead, we asked employees to answer four questions related to adherence in the follow-up survey: “How many times did you read the LINE message?” “How many times did you visit the website?” “Did you visit other websites when you received a notification on LINE?” and “Did you read other related articles in the website?”.

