### Analysis

#### Sample size

As this is a feasibility study, a formal sample size calculation is not required [35], but we set the target sample size to maximum of 10 companies (200 employees), giving the variety of characteristics of the MSEs. We discussed with stakeholders, who collaborate the next definitive trial, about that this size is enough to proceed to it and agreed. This study protocol also aims to inform sample size in our future definitive trial, while the effect size estimates of feasibility study can be deviated [65]. This study protocol will support our decision to proceed to the next large trial and will be utilized for our revisions to the program and implementation strategy.

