#### Analysis of other quantitative data

Health outcomes will be evaluated using a paired *t*-test between pre-(T1) and post-intervention (T2) according to protocol. The effect sizes and 95% CIs will be calculated using Cohen’s *d* only for those who completed the post-intervention questionnaire. For subgroup analysis, we will conduct the same analysis in the subgroup divided by program completion (completer/non-completer) and satisfaction (satisfied/unsatisfied). Statistical significance will be defined as *P* < 0.05. IBM SPSS Statistics® version 28 will be used for all analyses.

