### Limitation

This study protocol has several limitations. First, the sample size may not be adequate to detect significant effectiveness in reducing psychological distress owing to the pilot nature of this study. Second, this study protocol lacks a control group; the true impact of the implementation strategy can only be determined in the next step. Third, generalizability of the study findings is limited owing to its challenges in the recruitment process. As with the definitive trial, only the MSEs which have high interests in health promotion can be the potential participants through the current recruitment process. Future studies could engage and recruit MSEs with low interests in health promotion may be required in studies with another research focus. Fourth, individual-level penetration may be affected by personal beliefs about mental health issues in the workplace (e.g., social desirability [71], fear of stigmatizations [72], concerns about negative impact at the workplace [73]). Thus, factors not related to the implementation strategy can be considered if the outcomes are evaluated. Fifth, digital interventions risk marginalizing vulnerable groups, such as people with difficulty using devices or without internet access. Ensuring the opportunity to provide the program for all employees is essential in future consideration. Sixth, we will not provide any additional supports to participants with high psychological distress since it is justified under the aim of primary prevention and the contents are relevant to reduce distress, but there still be a potential risk to make conditions worse. Seventh, this feasibility study will collect many exploratory items from participants to utilize the findings in future implementation research. Still, it may cause participants’ burden, resulting in the response bias. Although authors limit the items to as few, the potential burden should be acknowledged. Eighth, fidelity of implementation strategies is evaluated using one simple question, instead of using systematic approach, such as a checklist. Other actions of employers/managers to be achieved through the online lecture should be defined after this feasibility trial to develop a checklist.

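### The no-harm objective on distress has no criterion, and the planned K6 analysis, a completer-only difference test without a control group, cannot establish absence of harm

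*Protocol article*

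**What the plan says.** Under Aims and objectives, the fifth objective is "To ensure no harm on psychological distress of the users". Neither there nor elsewhere does the article attach a margin, a deterioration threshold or a decision rule to it.

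The analysis that covers K6 is in Analysis of other quantitative data: "Health outcomes will be evaluated using a paired" t-test between T1 and T2. "Statistical significance will be defined as *P* < 0.05". An interval is planned as well: "The effect sizes and 95% CIs will be calculated using" Cohen's d, "only for those who completed the post-intervention questionnaire". That restriction is written for the effect sizes and intervals, but a paired test needs T2 data in any case.

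Other harm data are described under Process outcome and in Table 2. Users answer five harm items, including one on mental symptoms, in the T2 questionnaire only. Employers/managers and recruiters rate one side-effect item at T2. For blocking of the LINE account, "We will assess this rate of blocking by system detection"; the harm assessment makes no use of it.

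On size, "we set the target sample size to maximum of 10 companies (200 employees"). The Limitation section says that "the sample size may not be adequate to detect significant effectiveness in reducing psychological distress". It also acknowledges that there is no control group, that highly distressed users get no added support, and that their condition could deteriorate.

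**The concern.** An objective that promises assurance of no harm needs an analysis that can rule out harm of a stated size. The planned test asks whether mean K6 changed at all. A result of P ≥ 0.05 in that test is compatible with no change and also with a worsening that the sample was too small to show.

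Two further gaps are separate from sample size. First, every user-reported harm measure depends on a T2 response. If users who felt worse are less likely to answer, the harm results come from a favourably selected group. The protocol has no data on whether that is so, but the plan contains no check on it. Second, a mean change near zero can hide a minority who deteriorate.

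At stake is the safety statement carried from this study into the planned cluster trial. The population deliberately includes people above the K6 threshold, and the protocol itself sees a risk that they get worse.

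**Working it through.** The article gives no power, SD, margin or expected T2 response for K6, so there is no figure of its own to reproduce. The following is an illustration.

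**Inputs from the protocol**
- 200 employees at most (Sample size), read here as invited employees.
- Expected participation 45–65%, target 60% (Implementation outcome, penetration).
- Alpha 0.05; sidedness is not stated and two-sided is assumed.

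**Assumptions not in the protocol**
- T2 response 50–100%.
- Pre-post correlation r of 0.5–0.7, with equal SD at both times.
- A worsening of 0.2 SD as the harm to be detected. This is illustrative only.

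**Formulas**
- Completers: n = 200 × participation × T2 response.
- Standardised change: dz = 0.2 / √(2(1 − r)). At r = 0.5, dz = 0.2, so 0.2 baseline SD equals 0.2 SD of change. At r = 0.7, dz = 0.2 / √0.6 = 0.258.
- Power: probability that a noncentral t with n − 1 degrees of freedom and noncentrality dz√n exceeds the two-sided 5% critical value. Miss = 1 − power.

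Check at n = 60, r = 0.5: dz√n = 0.2 × 7.746 = 1.549. The normal approximation gives Φ(1.549 − 1.960) = 0.341; the exact value is 0.331, a miss of 66.9%.

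| Participation | T2 response | n | Miss, r = 0.5 | Miss, r = 0.7 |
|---|---|---|---|---|
| 45% | 50% | 45 | 74.1% | 60.5% |
| 60% | 50% | 60 | 66.9% | 49.7% |
| 45% | 100% | 90 | 53.3% | 32.2% |
| 60% | 100% | 120 | 41.6% | 19.9% |
| 65% | 100% | 130 | 38.1% | 16.8% |

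The range is therefore about 17% to 74%. With 60–90 pairs (120 registrants, 50–75% response) and the effect set at 0.2 SD of change, the miss is 53–67%. If the 200 are read as users instead, with all answering, n = 200 and the miss falls to 20% (r = 0.5) or 5% (r = 0.7).

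**What the planned interval could exclude.** The half-width of the 95% interval for mean change, in baseline SD, is t × √(2(1 − r)) / √n:

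| n | r = 0.5 | r = 0.7 |
|---|---|---|
| 60 | 0.258 | 0.200 |
| 90 | 0.209 | 0.162 |
| 120 | 0.181 | 0.140 |

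So with an observed change of exactly zero and 60 completers, the upper limit is 0.20 to 0.26 SD. To exclude 0.2 SD with 80% power when the true change is zero (one-sided 0.025) takes 199 completers at r = 0.5 or 120 at r = 0.7. The protocol's participation range gives 200 × 0.45 = 90 to 200 × 0.65 = 130 registrants before any T2 loss. The first requirement is out of reach. The second is met only if nearly all answer (120/130 = 92% at the top of the range).

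**Selection, apart from power.** Overall mean change = response × change in responders + (1 − response) × change in non-responders. If responders show zero change, an overall worsening of 0.2 SD arises when non-responders worsen by 0.2/(1 − 0.5) = 0.4 SD at 50% response, or 0.2/(1 − 0.75) = 0.8 SD at 75%. A completer analysis would show none of it.

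Correlation of change within companies, which the paired t-test ignores, would usually lower precision further; it is not included above.

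**The case against.** The strongest reply is that the protocol never says how it will conclude on harm. A reader might infer that P ≥ 0.05 will be reported as no harm and that the team will scale up on that result. The text does not support either step. No section equates non-significance with safety, a 95% interval is planned alongside the P value, and progression depends on penetration alone, so a K6 result does not trigger the next trial. This stands, and the point must be limited accordingly.

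A second reply is that harm is not judged on K6 alone. There are user harm items, a side-effect rating by employers/managers and recruiters, system-detected blocking, and a statement in the Discussion that adverse events will inform the strategy before the full trial. This stands in part. The employer and recruiter ratings do not need a user's T2 response, but they are general judgements, and users' distress is not disclosed to the company. Blocking is recorded but not linked to harm.

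A third reply is that a margin may be in an unseen analysis plan. A missing margin alone would indeed be no finding. The article, however, fixes the objective, test, alpha and completer set for the effect estimates, and these do not fit together whatever the margin.

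Finally, the limitations are openly disclosed. They are, but the sample-size caveat concerns showing a reduction in distress; it says nothing on detecting or excluding a worsening.

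**Conclusion.** The point holds in a limited form. The objective is worded as an assurance, and the only K6 analysis is a difference test with an interval in T2 completers and no comparator. That cannot establish absence of harm, and users who worsened and did not respond are missing from every user-reported harm result.

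The mismatch of objective and analysis does not depend on any assumed number. The size does. A miss rate of 17% to 74% for 0.2 baseline SD rests on 200 being invited employees and on assumed T2 response and correlation. A single headline such as a miss two times in three is one corner of that range (about 60 completers at r = 0.5) and should not be quoted alone. That worse-off users are likelier to be lost is plausible but not shown in the document.

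Severity is moderate: this is the last of five objectives in a feasibility study whose primary outcome is penetration, and several of the limits are already disclosed.

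**What to change.** 1. Reword the fifth objective as estimating change in K6 and screening for a harm signal.
2. Base the harm statement on the upper limit of the 95% interval for mean K6 change, reported in K6 points as well as Cohen's d, and not on the P value. State no worsening beyond a given amount only against a margin that the sponsor justifies in advance; the 0.2 SD above is not a proposal. Say that without a control group the change cannot be attributed to the program.
3. Report the number and percentage who deteriorate by a K6 point change fixed in advance. Crossing from below 5 to 5 or more should not be the sole measure, because it cannot register worsening in people who start at 5 or above.
4. Report T2 non-responders and system-detected blockers with all registrants as the denominator, and compare their baseline K6 with that of responders.
5. Add a sensitivity analysis over a range of assumed K6 changes in non-responders. Counting all of them as worsened is uninformative as the only analysis: at 50–75% response it makes 25–50% worsened by construction.

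The cost is wording and a few more tables from data already to be collected. The downside is a weaker safety statement.
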